#### Secondary outcomes

2. Improvements in child and primary parent functioning at 3 and 6 months post-randomisation.

We also aim to assess whether the brief sleep intervention is cost-effective when compared with TAU.

We hypothesise that compared with a TAU comparison group, children with ASD who receive the *Sleeping Sound* intervention will show greater improvements at 3 months post-randomisation (postintervention; primary outcome time point) and at 6 months post-randomisation in the following areas:

Reduction in overall child sleep problems.Decreased daytime sleepiness by teacher report, and improvements in sleep hygiene and sleep disturbances by parent report;Decreased emotional and behavioural problems reported by parents and teachers;Decreased social-communicative symptoms reported by parents;Increased cognitive performance, academic achievement and school attendance;Increased child quality of life reported by parents;Decreased parent stress and mental health symptoms;Increased parent quality of life and work attendance.

We also hypothesise that the behavioural sleep intervention will be a cost-effective treatment when compared with TAU from a societal and healthcare perspective. Thus, we will compare the costs and benefits (expressed in quality-adjusted life-years (QALYs)) between the two arms of the trial over the period of the study (further details are provided below).

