### Economic evaluation

An important secondary aim of the project will be to determine the cost-effectiveness of this intervention compared with TAU. The inclusion of the Child Health Utility 9D at baseline, 3-month and 6-month follow-up will allow calculation of QALYs as part of a cost–utility analysis, applying the area-under-the-curve approach.^62^ A supplementary cost-effectiveness analysis will also be undertaken using the total CSHQ score as an outcome measure. The economic analysis will be conducted from a societal perspective, since interventions targeting children with ASD are likely to have benefits and costs beyond the narrow health sector (eg, ASD intervention services and productivity impacts for parents). A secondary analysis from a healthcare perspective will also be undertaken. The evaluation will first measure and value the use of healthcare resources over the period of the study between the two arms of the trial and then compare any additional costs to the additional outcomes achieved. Costs of the intervention will be measured using the financial records of the study team. Other costs incurred by children and their families will be measured using a Resource Use Questionnaire. Components of the Resource Use Questionnaire comprise the child’s use of healthcare services, including: (1) inpatient services and emergency services, (2) health professional visits, (3) medication and (4) other resources used. The questionnaire also collects data on out-of-pocket and travel costs, as well as on a child’s school attendance and parent’s productivity. Participants will also be asked for their permission to access their MBS and PBS data for a time period of 3 months prior to baseline up until the last follow-up assessment. These data are not subject to recall bias and provide complete resource use costs (and out-of-pocket costs) for all MBS and PBS reimbursed healthcare services. Non-MBS and non-PBS funded services (eg, state-funded ASD services) will be captured in the Resource Use Questionnaire. Generalised linear models will be used to assess mean difference in costs and outcomes between the two arms, adjusted for any differences between groups at baseline. An incremental cost-effectiveness ratio and an incremental cost–utility ratio will be calculated as the difference in average cost between the groups, divided by the difference in average CSHQ and QALYs, respectively. Non-parametric bootstrapping will be undertaken from the observed cost/QALY pairs (1000 simulated replications) to determine CIs and presented in a cost-effectiveness plane along with a cost-effectiveness acceptability curve. Sensitivity analyses will be carried out to explore the robustness of the results. While MBS and PBS data will be used for the base case analysis, a sensitivity analysis will be performed using self-report data derived from the Resource Use Questionnaire for those health services not captured by MBS and PBS.

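### As worded, the economic base case leaves health services outside MBS/PBS to a sensitivity analysis, which conflicts with the stated societal and healthcare perspectives

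*Protocol article*

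**What the plan says.** All but one of the statements below are in the Economic evaluation section of the protocol article.

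- **Main perspective:** "The economic analysis will be conducted from a societal perspective". The reason given is that there are likely to be "benefits and costs beyond the narrow health sector (eg, ASD intervention services and productivity impacts for parents".
- **Second perspective:** "A secondary analysis from a healthcare perspective will also be undertaken". The hypotheses under Secondary outcomes match this: the intervention is expected to be a "cost-effective treatment when compared with TAU from a societal and healthcare perspective".
- **Cost sources:** intervention costs come from the study team's financial records. For the rest, "Other costs incurred by children and their families will be measured using a Resource Use Questionnaire". The questionnaire covers inpatient and emergency services, professional visits, medication and other resources, and also out-of-pocket costs, travel, school attendance and parent productivity.
- **Reach of the linked data:** MBS/PBS data are described as complete, but for services reimbursed by those two schemes. For the remainder, "Non-MBS and non-PBS funded services (eg, state-funded ASD services) will be captured in the Resource Use Questionnaire".
- **Base case:** the closing sentence assigns MBS and PBS data to the base case and then says a "sensitivity analysis will be performed using self-report data derived from the Resource Use Questionnaire for those health services not captured by MBS and PBS".

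**The concern.** A perspective determines which costs belong in the total. A healthcare total needs all health services used, whoever funds them. A societal total needs those and more. The closing sentence instead sorts costs by data source: linked data go to the base case, and self-report on health services that the linked data miss goes to a sensitivity analysis. Taken at its word, this puts a cost category required by both stated perspectives outside the main result.

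The incremental ratios are at stake, and so are the cost-effectiveness plane and acceptability curve if they are built on base-case costs. If the intervention changes how families use services outside MBS/PBS, the headline analysis would not register it. An unclear base case also leaves room to choose the cost total after results are known. The point concerns which cost categories enter the base case. It does not concern which families consent to data linkage.

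**Working it through.** The plan gives no unit costs, mean costs or expected QALY difference, so there is no figure of its own to reproduce. The check is a comparison of the text, followed by the algebra of what is left out.

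**Step 1. Place each cost category under the wording as it stands.**

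| Cost category | Source named | Needed for healthcare view | Needed for societal view | In base case as worded |
|---|---|---|---|---|
| Intervention | Study financial records | Yes | Yes | Yes; nothing removes it |
| Services funded by MBS/PBS | Linked data | Yes | Yes | Yes |
| Health services outside MBS/PBS | Questionnaire | Yes | Yes | No; sensitivity analysis |
| State-funded ASD services | Questionnaire | Depends on classification | Yes | Unclear; depends on whether they count as health services |
| Travel, out-of-pocket, productivity | Questionnaire (linked data also give out-of-pocket costs for scheme-funded services) | Not the issue here | Yes | Not removed by the sentence |

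The third row is the conflict, and the fourth may add to it. No other section of the article puts either row into the base case. Which inpatient or emergency services fall outside MBS/PBS is not stated, so the third row cannot be itemised further.

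**Step 2. Write out the difference.** With Δ for intervention minus TAU:

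ΔC(societal) = ΔC(intervention) + ΔC(MBS/PBS) + ΔC(outside MBS/PBS) + ΔC(travel, out-of-pocket, productivity)

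The base case as worded drops the third term. Its ratio therefore differs from the stated one by

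ΔC(outside MBS/PBS) / ΔQALY,

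or the same numerator over ΔCSHQ for the supplementary analysis. The same term is missing from the healthcare total. The error is zero if ΔC(outside MBS/PBS) = 0, that is, if the arms use these services equally.

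**Step 3. Sensitivity of the ratio, on assumed inputs only.** The plan computes QALYs by area under the curve from CHU9D at baseline, 3 and 6 months. Assume equal baselines and a constant utility gain g at 3 and 6 months, with each interval lasting 0.25 year:

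ΔQALY = 0.5 × g × 0.25 + g × 0.25 = 0.125g + 0.25g = 0.375g

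For an assumed $100 per child of between-arm difference in the omitted services:

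| Assumed g | ΔQALY = 0.375g | Shift in ratio = $100 / ΔQALY |
|---|---|---|
| 0.01 | 0.00375 | about $26,700 per QALY |
| 0.02 | 0.0075 | about $13,300 per QALY |
| 0.04 | 0.015 | about $6,700 per QALY |

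This shows only that a six-month QALY denominator is small, so any cost term left out has leverage. Neither g nor the $100 comes from the document, and any other $100 item would move the ratio equally.

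**The case against.** The best defence is that the closing sentence is loosely worded and the costing plan behind it is sound. The section prefers linked data because they are free of recall bias, and it says without restriction that the questionnaire captures services outside the schemes. The authors may have meant linked data where available, questionnaire data elsewhere, and a sensitivity analysis on self-report. The article is also condensed, and itemised costing usually sits in a fuller plan.

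Part of this stands. The intended analysis may well be right, and unit costs and item lists are properly left to another document. But the article does state a base-case rule, and that rule names self-report for services the schemes do not capture, which is not a swap of data source. The sentence needs correcting even if the intention was sound.

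A reader might also infer four stronger conclusions that the document does not support:

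- *The societal perspective is abandoned.* The sentence moves only health services outside MBS/PBS. Parent productivity, one of the two examples given for the societal view, is not removed, nor are travel and out-of-pocket costs.
- *ASD intervention services are definitely left out.* The section presents them as lying beyond the narrow health sector, so they may not be among the health services that are moved. Their status is unclear.
- *The sensitivity analysis is useless if those services are already in the base case.* Showing results with and without recall-based costs could have some value, so this goes too far.
- *The incremental cost will have the wrong sign.* That would require the arms to differ enough in the omitted services, and nothing in the document shows that they would.

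**Conclusion.** The concern holds as a conflict between a stated rule and the stated perspectives. As worded, the base case excludes health services outside MBS/PBS, which the main societal and secondary healthcare analyses both require, and it leaves the place of state-funded ASD services open. The conclusion rests on reading the closing sentence literally and on the absence of any other statement that restores these costs.

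The size and direction of any bias cannot be determined from the document. The bias equals the between-arm difference in the omitted costs over the difference in effect, and it is zero if use is balanced. The dollar figures under the check are illustrations. The point affects the cost-effectiveness aim, which the article calls an important secondary one. It does not touch the primary CSHQ comparison. It is worth correcting before the economic analysis is run.

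**What to change.** Reword the last sentence of Economic evaluation along these lines:

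- **Base case, societal:** intervention cost; MBS/PBS data for the services those schemes cover; questionnaire data for all services they do not cover, counted once only; plus travel, out-of-pocket and productivity costs.
- **Healthcare perspective:** the health-service parts of the same total, including questionnaire-reported health services outside MBS/PBS. State whether state-funded ASD services count as health services here.
- **Sensitivity analysis:** replace MBS/PBS costs with questionnaire self-report for the services that both sources cover, which tests the data source. A version that excludes recall-based costs can be shown in addition.

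No new data are needed. Table 3 has parent-reported service use at baseline, 3 and 6 months, each over the preceding 3 months, and the article describes follow-up as still under way when it was written. The work is wording, unit costs for the questionnaire items, and a rule against double counting. The small downside is that part of the base-case cost then rests on 3-month parent recall and is noisier.

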
## Ethics and dissemination

Behavioural sleep problems are a common burden associated with ASD. The proposed RCT of the *Sleeping Sound* intervention in ASD children with sleep problems will result in a significant advance in research on the treatment of sleep problems. The study is well-justified with reference to the demonstrated success of this tailored sleep intervention in ADHD,^47^ our strong pilot data,^48^ and the potential advantages of the intervention in alleviating social, emotional and academic problems connected to the sleep disorder in the children themselves and their parents. If the intervention is found to be effective in this sample of children who are of borderline/average intellectual ability, we will subsequently be able to explore whether the intervention is successful for children with ASD who also have an intellectual disability. Treatment recommendations for treating sleep problems in children with ASD have been released.^63^ The Sleep Committee of the Autism Treatment Network recommend the use of behavioural intervention as a first-line therapy.^64^ The Autism UK National Institute for Health and Care Excellence clinical guidelines (No 170) for sleep management recommend development of individualised behavioural intervention which includes specialist monitoring and use of a sleep plan as a central concept of sleep management.^65^ To date, the treatment of sleep disturbance in children with ASD is based on expert opinion and consensus practise, informed by limited evidence. Results from this study will inform evidence-based clinical practice and guide appropriate selection and tailoring of behavioural strategies to address specific sleep problems. We aim to publish our findings in peer-reviewed journals and present our research at international conferences and community organisations. The study has been granted ethical approval by the Royal Children’s Hospital (No 36154), Deakin University (No 2017–130), the Victorian Department of Education and Early Childhood Development (No 2016_003134) and the Catholic Education Office (Melbourne No 0501) Human Research Ethics Committees. Important protocol changes are reported to each ethics committee via ethics amendments.

## Data management

All participant data will be confidential and hardcopy data will be securely stored in locked offices for which only research team members have access to the keys. All online participant data are collected and stored in REDCap,^54^ which is a secure database stored on the Deakin University network, accessible only to the research team via individual usernames and passwords. All chief investigators will have access to the final dataset. Information will be kept for 7 years after the youngest participant’s 18th birthday or 15 years after the completion of the study, whichever date is later. After this time, the data will be destroyed.

Data from all hardcopy surveys will be entered into REDCap by a member of the research team.^54^ To ensure quality data, a process of data checking and cleaning will be undertaken by the research team. We will keep a register of data issues to ensure problems with data are addressed in a timely manner and conduct regular audits of data management processes.
